### Sample size

Our power calculations will be based on the following:A previously calculated metastasis incidence of 60% 5 years following diagnosis for individuals not taking melatonin (participants in the control group). This is a relevant calculation considering the high-risk population recruited based on our inclusion criteria [46–49].An earlier study which included study participants with surgically removed lymph node metastases of malignant melanoma which showed that 31% (5 of 16 participants) of those treated with 20 mg of evening melatonin developed distant metastases compared to 71% (10 of 14 participants) of those not treated with melatonin [8].

Based on this previous research, the following assumptions are made:The number of participants in the melatonin group which will have developed distant metastases after 5 years: 30%The number of participants in the control group which will have developed distant metastases after 5 years: 60%.Alpha: 0.05Beta: 0.2Power: 80%Results: 42 participants must be included in each group, i.e., both the melatonin and the control group, in order to achieve statistical significance (Table 3). To obtain a safety margin in case some participants withdraw from the trial, we will strive after a group population of 50 participants per group.

**Table 3 Tab3:** Power calculation

**Melatonin, *****n***** = **	42
**Control, ***n*** = **	42
**Incidence, melatonin group**	30%
**Incidence, control group**	60%
**Alpha**	0.05
**Beta**	0.2
**Power**	0.8

### Outcomes

The primary outcome is the number of patients which develop metastasis in the melatonin group vs. the control group. This will be evaluated as a relative risk (RR), with a 95% confidence interval. The secondary outcomes include the following: Overall survival 5 years from randomization in the melatonin group vs. control group, evaluated with Kaplan-Meier curves and the Log-rank test.Overall survival after detection of metastases in the melatonin group vs. control group, was evaluated with Kaplan-Meier curves and the Log-rank test.Hazard for having developed other cancers within 5 years from randomization in the melatonin group vs. control group, evaluated as Cox regression hazard ratio (HR).Number of patients with AE and SAE in the melatonin group vs. control group, assessed by CTCAE and evaluated as relative risk (RR) with a 95% confidence interval.

Other outcome measures:Interim analysis: number of patients developing metastasis within 3 years in the melatonin group vs. control group, evaluated as relative risk (RR), with 95% confidence interval.Interim analysis: overall survival in 3 years in the melatonin group vs. control group, evaluated with Kaplan-Meier curves and the Log-rank test.

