### In the event of detection of metastases

If a suspected metastasis is detected in radiological examinations and then verified with a biopsy, the patient will be referred by their physician to an oncology clinic in their home region. This is a standard clinical routine and will not be impacted by this trial. The oncology clinic will make a decision regarding next steps to investigate, examine, and treat the metastases. Patients with metastases typically receive systemic chemotherapy, immunotherapy with so-called checkpoint inhibitors, and/or regional perfusion treatment of the liver where high doses of chemotherapy are injected into the liver’s circulatory system. These treatments are demanding for patients and can result in side effects such as fatigue, susceptibility to infection, dry mucous membranes, and pain. The average survival following metastasis detection is about 1 year. Metastasis detection does not alter the melatonin doses or treatment instructions in this trial. Melatonin given at a dose of 20 mg at 10 pm has shown particularly positive effects in advanced stages of cancer in earlier studies [10].

It has also been reported that systemic chemotherapy is more easily tolerated in patients who are simultaneously treated with melatonin, particularly in regard to neurotoxicity, thrombocytopenia, weight loss, and asthenia [44]. Furthermore, there are fewer cases of alopecia (hair loss) and infection in patients taking 20 mg of melatonin at 10 pm while undergoing radiotherapy [45]. If participants in this trial take melatonin from the time that their metastases are detected, the metastases will be included in both the intention-to-treat and the per-protocol analysis. Survival in the melatonin group following metastasis detection will therefore be counted in the patients still taking melatonin.

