#### Clinical safety

Our outcomes for clinical safety will be the number of adverse events (AE), the number of serious adverse events (SAE), and the number of suspected unexpected serious adverse reactions (SUSAR) in the melatonin group and control group respectively. These will be measured through data collected from CRF forms and patients’ chart documentations. The subjects are encouraged to contact us if they experience side effects, or new or worsened symptoms. They will be asked about AE and SAE at 3 months and 1 year after starting melatonin treatment, and thereafter every 6 months until 5 years have passed since recruitment.

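### Harms are compared only as a crude 5-year relative risk, which under the plan's own assumptions moves with efficacy even when melatonin has no effect on adverse events

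*Protocol article*

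**What the plan says.** The Outcomes section of the protocol lists the harm outcome as "Number of patients with AE and SAE in the melatonin group vs. control group, assessed by CTCAE and evaluated as relative risk (RR"); the interval is to be at the 95% level. The Clinical safety section describes it as counts: "Our outcomes for clinical safety will be the number of adverse events (AE), the number of serious adverse events (SAE") and SUSARs per group, with patients questioned "thereafter every 6 months until 5 years have passed since recruitment". Neither section gives a person-time denominator or says how death enters the comparison. Another secondary outcome in the same list does get a time-to-event measure: "Hazard for having developed other cancers within 5 years from randomization in the melatonin group vs. control group, evaluated as Cox regression hazard ratio (HR").

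The planning figures are in the Sample size section: "The number of participants in the control group which will have developed distant metastases after 5 years: 60" per cent, and "The number of participants in the melatonin group which will have developed distant metastases after 5 years: 30" per cent. On survival once metastases are found, the section on detection of metastases says "The average survival following metastasis detection is about 1 year", the Abstract gives a median of 1 year, and the Introduction gives a median of 1 to 2 years. The Harm section names death among the SAE criteria and states no exemption for death from the disease.

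**The concern.** New adverse events can be recorded only while a patient is alive and in follow-up. If melatonin works as assumed, the arms differ in three ways that have nothing to do with drug toxicity: controls live for less of the 5 years, spend less time free of metastases, and spend more time with metastases and their systemic treatment. A proportion of randomised patients with an event mixes all three with any real effect of melatonin on adverse events. The first two raise the melatonin-to-control ratio and the third lowers it. If disease deaths count as SAEs, the ratio for SAEs falls further. Melatonin's low toxicity is central to the protocol's benefit-risk argument, so its one named harm comparison should be readable apart from efficacy.

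**Working it through.** **Plan's own figure.** Sample size gives "Alpha: 0.05Beta: 0.2Power: 80" per cent, with 30% against 60%. Two-sided, pooled variance, mean proportion 0.45: n = [1.96·√(2·0.45·0.55) + 0.842·√(0.6·0.4 + 0.3·0.7)]² / 0.3² = 41.97. The stated 42 per group is reproduced, so 60% and 30% are the operative planning risks.

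**Assumptions not in the protocol.** It does not state when metastases occur. I assume a constant metastasis hazard λ = −ln(1−p)/5, a constant death hazard μ after metastasis, and no other deaths.
- Control: λ = −ln(0.4)/5 = 0.183 per year.
- Melatonin: λ = −ln(0.7)/5 = 0.071 per year.
- 1-year median survival: μ = ln 2 = 0.693 per year.

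**Time under observation.** Metastasis-free time is p/λ. The proportion alive is S(t) = e^(−λt) + [λ/(μ−λ)]·(e^(−λt) − e^(−μt)), integrated from 0 to 5.

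| 1-year median | Control | Melatonin |
|---|---|---|
| Years alive | 3.95 | 4.53 |
| Years metastasis-free | 3.27 | 4.21 |
| Years with metastases | 0.67 | 0.32 |
| Dead by year 5 | 47% | 22% |

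Controls have 1 − 3.95/4.53 = 12.8% less time alive and about 2.1 times the time with metastases.

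| Less time alive in controls | Constant hazard | Uniform timing over 5 years |
|---|---|---|
| Mean survival 1 year | 15.0% | 11.3% |
| Median 1 year | 12.8% | 9.6% |
| Median 2 years | 8.5% | 6.3% |

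**Crude relative risk, same event rate r in both arms.** Risk = ∫ r·e^(−rt)·S(t) dt from 0 to 5, constant hazards.

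| r per year | Median 1 year | Median 2 years |
|---|---|---|
| 0.01 | 1.15 | 1.09 |
| 0.1 | 0.360/0.319 = 1.13 | 1.08 |
| 0.2 | 1.11 | 1.07 |
| 1 | 1.04 | 1.02 |
| 2 | 1.01 | 1.01 |

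At rates up to 0.2 the widest values are 1.17 (mean survival 1 year) and 1.05 (uniform timing, median 2 years).

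**Event rate five times higher after metastasis (assumed), no drug effect.** At r = 0.01 to 0.2 the crude ratio is 0.88 to 0.97 (median 1 year) or 0.80 to 0.93 (median 2 years). The person-year ratio over all time alive, median 1 year, is [(4.206 + 5·0.322)/4.528] / [(3.274 + 5·0.674)/3.948] = 1.284/1.683 = 0.76. Cutting time and events at metastasis leaves rate r in both arms, so the ratio is 1.00.

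**Disease deaths counted as SAEs.** Risk = 1 − e^(−5r)·S(5). At non-fatal rates of 0.05, 0.1 and 0.2 per year the ratio is 0.68, 0.78 and 0.89 (median 1 year) or 0.71, 0.82 and 0.91 (median 2 years). If melatonin truly raised the non-fatal rate by 50%, the 1-year-median ratios would still be only 0.80, 0.94 and 1.03.

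**Sampling error.** With 50 per arm and risks of 0.319 and 0.360, the 95% CI factor is exp[1.96·√(0.681/(50·0.319) + 0.640/(50·0.360))] = 1.7 each way. At r = 0.05 it is about 2.3.

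**The case against.** The proportion of patients with an event within 5 years of assignment is a legitimate intention-to-treat quantity, and exposure-adjusted rates are often added in an analysis plan that is not shown here. The Statistical analysis section also names the log-rank test for the secondary objectives in general. That stands as a reason to keep the relative risk. It does not remove the point, because Outcomes fixes one measure for harms and that measure is the one that moves with efficacy.

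The shift is small: it nearly vanishes for frequent events, which any-AE over 5 years may well be, and it lies inside the confidence interval at 50 per arm. That also stands. Its direction, however, is set by efficacy rather than by chance.

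A reader might infer that the relative risk should simply be replaced by a rate per year alive. The working does not support this: with a higher event rate after metastasis, that ratio (0.76) lies further from 1 than the crude one (0.88 to 0.97), because it corrects for time alive but exposes the difference in metastatic time. Cutting at metastasis has its own cost. Melatonin continues after detection, so on-drug events are left out, and the cut is at a post-randomisation event that treatment is assumed to affect.

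**Conclusion.** The point holds in a limited form. With no drug effect on events, the crude relative risk departs from 1 by an amount that depends on efficacy: about 1.07 to 1.15 for uncommon events with a 1- to 2-year median and constant hazards, near 1 for common events, about 0.80 to 0.97 with an assumed fivefold rate after metastasis, and about 0.68 to 0.91 for SAEs if disease deaths count. All of this rests on the 60% and 30% planning risks and on an assumed timing of metastases.

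Two stronger readings are not supported. The first is that the protocol itself implies 13% less observation in controls. That is one scenario (constant hazards, 1-year median) in a range of roughly 6% to 15%. The second is that longer survival necessarily inflates melatonin's SAE ratio. If disease deaths count, the ratio moves the other way, and the Harm section's wording on death, which ties it to a dose, leaves open whether they do.

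**What to change.** In Outcomes and Statistical analysis, keep the 5-year relative risk as the intention-to-treat summary and add beside it, for AEs and for SAEs, the rate ratio per person-year (or the first-event hazard ratio) with 95% CI:

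1. with time and events cut at metastasis detection in both arms, as the comparison least affected by metastatic disease and its treatment;
2. over all time alive and in follow-up, labelled as still reflecting treatment of metastases.

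State whether deaths from uveal melanoma count as SAEs, and show the SAE result without them.

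Cost: mainly wording, with no added visits. The first analysis leaves out on-drug events after metastasis and censors at a post-randomisation event, which is why the relative risk and the second analysis stay. Metastasis and death are already taken from patient charts. The Harm section's list of what is registered for each AE does not mention an onset date, so the CRF must capture one.

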#### Clinical effects

Our primary and secondary outcomes for the clinical effects of melatonin treatment will be performed through data collected from patient charts, where it is registered if the subject has developed metastasis, if they are deceased, and/or if they have received another cancer diagnosis in addition to uveal melanoma.

#### Clinical safety

Our outcomes for clinical safety will be the number of adverse events (AE), the number of serious adverse events (SAE), and the number of suspected unexpected serious adverse reactions (SUSAR) in the melatonin group and control group respectively. These will be measured through data collected from CRF forms and patients’ chart documentations. The subjects are encouraged to contact us if they experience side effects, or new or worsened symptoms. They will be asked about AE and SAE at 3 months and 1 year after starting melatonin treatment, and thereafter every 6 months until 5 years have passed since recruitment.

### End of study definition

The trial will be terminated when the last participant in this trial has had their 5-year control (Last Subject Last Visit (LSLV)). No further treatment or contact with the participants will be made after this point of time.

### Statistical analysis

We will be analyzing our data according to “intention to treat” where all participants randomized to either the melatonin or control group are included in the said group even if some terminate their participation in the trial or are excluded from the trial later on. We will at the same time analyze our data “per protocol” where the participants who terminate their participation during the trial or are noncompliant to melatonin treatment are excluded from the analysis.

To answer our primary and secondary objectives, we will use both the chi-square test and the Log-rank test of cumulative survival with associated 95% confidence intervals and *p*-values. Relative risk will be calculated as the probability of metastasis in the melatonin group divided by the risk of metastasis in the control group.

*P* values less than 0.05 will be considered significant, and all tests will be double-tailed, or two-sided.The Shapiro–Wilk test will be used to confirm if our continuous data is normally distributed.A Student’s *t*-test will be used to compare the differences in normally distributed continuous data within the melatonin and control groups, respectively. Data found not to be normally distributed data will be compared using the Mann–Whitney *U*-test.In order to compare the risk of death and metastasis between the melatonin and control group, we will also use a Cox Regression, adjusted for covariates such as tumor size, T category, cell type, presence of extra scleral growth, presence of extracellular matrix patterns, and BAP-1 expression.

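### The 5-year relative risk is the primary measure, but no single test or analysis set is named to decide it, and later withdrawals have no known 5-year status

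*Protocol article*

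**What the plan says.** The primary measure is clear. The Abstract, Study objectives and hypothesis, and Outcomes all name the relative risk of metastasis at 5 years; Outcomes adds "This will be evaluated as a relative risk (RR), with a 95% confidence interval". Statistical analysis defines the estimator: "Relative risk will be calculated as the probability of metastasis in the melatonin group divided by the risk of metastasis in the control group". The Sample size section compares two proportions, 30% and 60%, and concludes that "42 participants must be included in each group", with 50 per group as a margin for withdrawals.

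The deciding analysis is less clear. Statistical analysis states: "To answer our primary and secondary objectives, we will use both the chi-square test and the Log-rank test of cumulative survival". It continues: "In order to compare the risk of death and metastasis between the melatonin and control group, we will also use a Cox Regression", with an open-ended list of covariates. ITT and per-protocol analyses are run side by side, p-values below 0.05 count as significant, and "all tests will be double-tailed, or two-sided". Neither the tests nor the sets are ranked. Table 1 lists both metastasis-free survival and the proportion with metastases for evaluation at year 5.

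On incomplete follow-up, the ITT set keeps all randomised participants, including those who later leave. The Withdrawal section ends data collection at withdrawal, keeps what was already collected, and replaces only those who leave within 6 months.

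**The concern.** There are two linked problems.

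First, the final metastasis question can be answered by chi-square, log-rank or Cox, in either of two sets. If these disagree, the article gives no rule for which result is the trial's answer. Reporting success on whichever crosses 0.05 would exceed the stated two-sided 5%. The Cox covariate list adds further freedom.

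Second, a ratio of crude 5-year proportions needs a 5-year status for everyone in the denominator. A participant who withdraws at 2 years without metastasis stays in the ITT denominator, but no later data are collected. The RR cannot be computed without assigning that person a status. The choice matters most if withdrawal differs by arm, which is plausible here: the trial is open-label and only one arm takes nightly tablets for 5 years. The per-protocol set does not solve this. It drops those who leave, and also those noncompliant with melatonin, which only one arm can be.

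**Working it through.** **1. The plan's own figure.** Inputs from Sample size: 60% v 30%, two-sided alpha 0.05, power 80%. With mean proportion 0.45,

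n = [1.960·√(2·0.45·0.55) + 0.842·√(0.6·0.4 + 0.3·0.7)]² / 0.30² = (1.379 + 0.565)² / 0.09 ≈ 42 per group.

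The stated 42 is reproduced (power 80.0%); 50 per group gives 86.6%. The sample size is correct and matches a comparison of two proportions.

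**2. False positives if any test may decide.** Simulated trials with no effect: 50 per arm, 60% metastasis at 5 years in both arms, exponential times, 10,000 trials per scenario. Assumptions not in the article: 5% death without metastasis, 0 to 20% withdrawal, equal in both arms, withdrawals scored metastasis-free in the chi-square test, and 10% of the melatonin arm (20% in one run) excluded from per-protocol as noncompliant.

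| Rule for claiming success | False-positive rate |
|---|---|
| ITT chi-square alone | 5.2 to 5.6% |
| ITT log-rank alone | 4.9 to 5.2% |
| Either ITT test | 6.5 to 7.2% |
| Either test, ITT or per-protocol | 7.8 to 9.4% |

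Simulation error is about half a percentage point: 1.96·√(0.07·0.93/10,000) = 0.005. A separate simulation of 20,000 trials, with 2% other-cause deaths a year and 20% of the melatonin arm excluded, gave 6.5% and 8.5% for the last two rows. Cox was not simulated. With equal withdrawal, the two ITT tests gave different conclusions in about 3 to 4% of null trials and 4 to 7% of trials under the design effect.

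**3. The crude RR if later withdrawals are scored metastasis-free.** This counting rule is an assumption, as are the withdrawal rates. There is no true effect.

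- *16% v 4% withdrawing, spread evenly over 5 years.* With exponential times, the chance that metastasis is seen before withdrawal is 1 − 0.6/0.9163 = 0.345, where 0.9163 = −ln(0.4). RR = (0.84·0.6 + 0.16·0.345)/(0.96·0.6 + 0.04·0.345) = 0.559/0.590 = 0.95.
- *16% v 4%, all at 6 months*, the earliest point not covered by replacement. The chance of metastasis by then is 1 − 0.4^0.1 = 0.088. RR = (0.504 + 0.16·0.088)/(0.576 + 0.04·0.088) = 0.518/0.580 = 0.89.
- *Constant withdrawal hazards with 5% death without metastasis.* The observed proportion is (m/s)·(1 − e^(−s)), where s = m + w + d, m = 0.9163, d = −ln(0.95) = 0.0513 and w = −ln(1 − withdrawal). Control at 5%: s = 1.019, proportion 0.575. Melatonin at 20%: s = 1.191, 0.536, RR 0.93. Melatonin at 30%: s = 1.324, 0.508, RR 0.88. Simulation gave 0.931 and 0.885. Chi-square rejected in 7.5% and 10.8% of null trials, against 5.1% and 4.6% for log-rank. Replacement within 6 months is not modelled in this case.
- *Equal withdrawal of 16%.* The crude proportion falls from 60% to about 55% in both arms and the RR stays at about 1.00. Under the design effect it is 0.495, against 0.50.

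**4. Does one time-to-event analysis fit the planned size?** If 8 of 50 per arm were lost completely, 42 would remain, which gives 80.0%. A censored analysis also uses their follow-up up to withdrawal. In simulation with 16% withdrawal per arm, power was about 84% for log-rank and 82% for crude chi-square.

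**The case against.** The strongest reply is that a primary measure already exists. Three sections name the 5-year RR, the sample size agrees with it, and Outcomes gives log-rank to overall survival and Cox to other cancers. On that reading the chi-square test serves the RR outcomes, the log-rank test serves survival, and Cox is an extra. This stands as far as the estimate goes, and a reader who inferred that the trial has no primary measure would be wrong. It does not settle the test or the set: the sentence in Statistical analysis assigns both tests to the primary objective, the Cox sentence names metastasis expressly, and nothing says whether ITT or per-protocol decides.

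A second reply is that metastasis status comes from registries and charts without active participation (Table 1, footnote b), so stopping tablets or missing calls need not lose the outcome. That is right for those still in the trial. It does not help after formal withdrawal, when collection stops.

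A third reply is that a fuller plan may hold a counting rule. A reader might infer that withdrawn participants are misclassified, but the article does not say how they are counted. The bias in the RR is therefore conditional. What the article does fix is a crude ITT proportion together with an end to data collection at withdrawal, and those two do not fit.

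**Conclusion.** The point holds in a limited form. The primary measure is fixed; the deciding test and analysis set are not. Left open, the false-positive rate for the final metastasis question is about 6.5 to 7% over the two ITT tests and about 8 to 9% with per-protocol added, given the assumed exclusion of 10 to 20% of the melatonin arm. The crude RR also needs an assumed status for withdrawals after 6 months. If that status is metastasis-free, unequal withdrawal would move a true RR of 1 to between about 0.95 and 0.88; equal withdrawal would hardly move it.

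Two stronger readings are not supported. One is that the plan expects 16% withdrawals: 8/50 is only the recruitment margin, and no rate is forecast. The other is a false-positive rate of about 14%, which results from adding the interim metastasis and overall survival tests. Overall survival is a different endpoint, Outcomes lists the interim analyses under other measures, and nothing allows a primary claim at that stage.

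**What to change.** Name one primary analysis: the ITT set, with the RR as the ratio of Aalen-Johansen cumulative incidences of metastasis at 5 years from randomisation. Treat death without metastasis as a competing event, censor withdrawals at their last scan, and give a 95% CI and one two-sided 5% test. Label the crude RR with chi-square, the log-rank test, the Cox model and every per-protocol analysis as supportive, with no separate claim.

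This keeps the planned RR and equals the crude RR when follow-up is complete. It is not the only valid choice (log-rank as the sole primary test would also settle which result decides), but it stays closest to the measure already fixed. Its weakness is that censoring must be assumed non-informative, which open-label withdrawal may violate. Add a sensitivity analysis that varies the outcome assumed for withdrawals in each arm.

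The cost is a few sentences and standard software, with no change in sample size. Because the trial is open-label, settle this before outcomes are compared by arm, including at the 3-year interim analysis.
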